### HT Group

In the HT group, the participants will receive 20 min high-frequency rTMS training intervention. The rTMS will be performed with a Super-Rapid Magstim Stimulator (The Magstim Co., Whitland, UK), including a figure-8 type coil. The reason why we chose the figure-8 type coil is not only because it has a stronger focus, but it reduces the risk of seizures and other side effects than the h-coil and circular type coil [29]. All of the rTMS program will be performed as the recommendations of the International Federation of Clinical Neurophysiology [30, 31]. The coil will be placed in the M1 area on the opposite side of the pain and uniformly in the left when the patient has bilateral knee pain, as in previous rTMS studies [32, 33]. To determine the coil position, we first will place the center of the helmet to install the figure-8 type coil at a point 1 cm lateral and 1 cm posterior from Cz. Then, we will identify the location and angle of the helmet by identifying the minimum stimulator intensity needed to cause a motor response in the targeted lower limb. We will keep the front surface of the helmet facing forward to ensure that the coil orientation is the same. The resting motor threshold (rMT) will be defined as the lowest intensity that produced five responses with peak-to-peak amplitude of at least 50mv in ten consecutive trials. We will determine the coil position and estimation of MT before the high-frequency rTMS session and the parameters are as follows: 10 Hz stimulation for 4 s per session, with a 40 s interval between sessions, 30 sessions per treatment, totaling 1200 pulses at 90% rMT over M1 of the target hemisphere.

### ST + Q Group

In the ST + Q group, sham rTMS will be delivered with the coil angle rotated 90° and only one wing of the coil touching the scalp of the participant to avoid inducing actual stimulation. The parameters, including noise, time, and frequency of the sham rTMS, will be the same as HT groups [34]. Each patient will receive sham rTMS daily for five consecutive days.

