**Methods:**

This study is an assessor-blind, sham-controlled, randomized controlled trial involving 12 weeks of intervention and 6 months follow-up. 148 participants with KOA will receive usual care management and be randomized into four subgroups equally, including quadriceps strength training, high-frequency rTMS training, sham rTMS and quadriceps strength training, high-frequency rTMS and quadriceps strength training. The rehabilitation interventions will be carried out 5 days per week for a total of 12 weeks. All outcomes will be measured at baseline, 4 weeks, 8 weeks, and 12 weeks during the intervention and 1 month, 3 months and 6 months during the follow-up period. The effectiveness outcomes will be included visual analog scale, isokinetic knee muscle strength, Knee Injury and Osteoarthritis Outcome score and 36-Item Short-Form Health Survey score; The act mechanism outcomes will be included motor evoked potential, grey matter density, white matter, subcortical nuclei volumes, cortical thickness and functional connectivity by MRI. Two-way of variance with repeated measures will be used to test the group and time effect for outcome measures.

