Non-invasive brain stimulation is an increasingly growing domain of rehabilitation therapeutics for clinical neurological disorders. A variety of techniques for transcranial brain stimulation has been proposed, such as, Transcranial Direct Current Stimulation (tDCS), Transcranial Magnetic Stimulation (TMS) [19]. A general opinion is that modulation of neuronal excitability by tDCS is a relatively simple function (e.g., cortical excitability is reduced by cathodal stimulation and increased by anodal stimulation) and tDCS effects are difficult to predict, rarely used to treat diseases with various neural circuits, such as, pain related to central sensitization [20]. For rTMS, the magnetic field pulse delivered by a stimulating coil applied on the scalp is able to pass through skull bone without being attenuated and to generate an electric field when entering the brain. The intensity of the induced current is sufficient to produce action potentials and to activate brain networks safely and painlessly [21]. rTMS has been proposed to treat various pain syndromes related to central sensitization phenomenon, a Level A of definite analgesic effect was stated for the use of high frequency rTMS of M1 applied contralaterally to the pain side in patients with neuropathic pain. Previous study demonstrated that the chronic pain associated with KOA may develop in connection with a maladaptive process of pain sensitization in the central nervous system [22]. Hence, there is a basis for speculation that rTMS could be beneficial in alleviating pain associated with KOA.

Although the positive rehabilitation effect of quadriceps strengthening and high-frequency rTMS for KOA have been demonstrated, respectively, the synergistic effect of the combination of the two for treat KOA is still unclear. Therefore, the randomized controlled trial is designed to observe whether high-frequency rTMS combined with quadriceps strength training can better improve the knee function and reduce pain in KOA patients than quadriceps strength training alone and explore the mechanism of this combined rehabilitation. The study will provide a new perspective on the treatment of KOA.

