**Table 1 Tab1:**
[figure not shown]
Schedule of enrolment, intervention and assessments

"√" means things will be done

*VAS* Visual Analog Scale, *TQPEAK* peak torque, *TQPEAK/BW* TQPEAK adjusted for body weight; agon/antag, agonist–antagonist ratio, *KOOS* Knee Injury and Osteoarthritis Outcome Score, *SF-36* 36-Item Short Form Survey, *GM* grey matter density, *WM* white matter, *FC* subcortical nuclei volumes, cortical thickness; functional connectivity

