### Allocation concealment and blinding

Allocation concealment will be performed by using sealed, opaque envelopes which will hide a serial number. Additionally, an independent study researcher will open the envelopes in sequence after participants complete all baseline assessments to avoid selective bias. Due to the visibility of the quadriceps strength training intervention, physiotherapists and patients cannot be blind to intervention allocation. Therefore, the blinding will only be applied to the assessors and statisticians who responsible for data collection and final statistical analyses in this study to avoid implementation bias and measurement bias. Importantly, they will not participate in the participant recruitment process.

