### Interventions

All participants will receive usual care management, including health education and physical therapy when necessary. Six qualified physiotherapists who have attained the physical therapist’s certification with over 5 years of experience will be trained beforehand to instruct and guide patients in carrying out these exercises. The interventions in four groups will be carried out 5 days per week for a total of 12 weeks.

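### The sham rTMS schedule is worded inconsistently: read literally, the ST + Q section gives 5 sham treatments, while the general rule for all four groups gives 60

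*Protocol article*

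**What the plan says.** The Protocol article describes treatment frequency in three places that bear on the sham.

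- Abstract, Methods: "The rehabilitation interventions will be carried out 5 days per week for a total of 12 weeks".
- Interventions, which names the arms collectively: "The interventions in four groups will be carried out 5 days per week for a total of 12 weeks".
- ST + Q Group, the only arm-specific statement of how often sham is given: "Each patient will receive sham rTMS daily for five consecutive days".

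Just before that last sentence, the ST + Q Group section says that the sham's noise, time and frequency are to match those of the HT group. The HT Group and HT + Q Group sections give no separate course length, so active rTMS follows the general rule. The QT Group section restates the full 12-week rule for quadriceps training.

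The Abstract calls the trial sham-controlled ("This study is an assessor-blind, sham-controlled, randomized controlled trial involving 12 weeks of intervention and 6 months follow-up") and sets the on-treatment assessments ("All outcomes will be measured at baseline, 4 weeks, 8 weeks, and 12 weeks during the intervention"). The Outcomes section puts the primary end-point at 12 weeks.

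**The concern.** The arm-specific sentence and the general rule do not give the same number of sham treatments. The sentence could describe the pattern within each week, or it could describe the whole sham course. A reader working from the ST + Q Group section alone could take it as the whole course, because a specific instruction is often held to override a general one.

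What is at stake is the comparison of HT + Q with ST + Q. It is the only contrast in the design that sets active against sham rTMS with quadriceps training the same on both sides. The primary effectiveness outcome is self-reported pain on a VAS, which is open to the effects of contact and expectation. A sham course much shorter than the active one would leave those effects mixed with the effect of stimulation in that contrast.

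**Working it through.** One treatment day is counted as one treatment. (The HT Group section uses the word session for a single 4-second train, so that word is avoided here.)

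**Inputs**

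- General rule: 5 days a week, 12 weeks (Abstract; Interventions).
- Sham sentence, literal reading: 5 days in total (ST + Q Group).
- Assessments at weeks 4, 8 and 12 (Abstract).
- Assumption for the literal reading: the five days fall within the first 4 weeks. The article does not say when they fall.

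**The plan's own figures.** The article states no total number of treatments, so there is none to reproduce. Its pulse count per active treatment does reproduce: 10 Hz × 4 s × 30 trains = 1200. That figure describes one treatment and says nothing about how many are given.

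**Treatments under the general rule:** 5 × 4 = 20 by week 4, 5 × 8 = 40 by week 8, 5 × 12 = 60 by week 12.

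| By week | Active rTMS in HT + Q | Sham, five days in each week | Gap | Sham, literal reading | Gap | Literal sham as share of active |
|---|---|---|---|---|---|---|
| 4 | 20 | 20 | 0 | 5 | 20 − 5 = 15 | 5/20 = 25% |
| 8 | 40 | 40 | 0 | 5 | 40 − 5 = 35 | 5/40 = 12.5% |
| 12 | 60 | 60 | 0 | 5 | 60 − 5 = 55 | 5/60 = 8.3% |

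On the literal reading, ST + Q would have no sham on 55 of 60 treatment days. The week-12 row needs only that the five days fall somewhere within the 12 weeks.

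**Which reading is likelier.** The general rule names all four groups, and no section gives a reason for a shorter sham course. The preceding sentence in the ST + Q Group section shows an intent to match sham to active delivery. All of this favours five days in each of the 12 weeks.

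**Why this does not settle it.** The HT Group section uses the term parameters for settings within a treatment: pulse rate, train length, interval and number of trains. On that usage, the matched frequency in the ST + Q Group section may be the pulse rate and not the number of treatment days. The schedule sentence then stands apart from it.

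**Effect on other figures.** The sample size calculation (116, raised to 148) takes no input from the number of treatments, so it is unaffected.

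**The case against.** The strongest reply is that there is no real conflict. The Interventions section gives days per week and duration for every arm, and the sham sentence can be read as adding only that the five days run consecutively within the week. Taken together they give 60. The literal reading needs one sentence to override, without comment, a rule that covers all four groups. Table 1, titled "Schedule of enrolment, intervention and assessments", is not shown here and may confirm the 12-week sham course. The text is also a journal article that condenses a fuller protocol.

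Most of this stands. It is why the weekly reading is taken as the likely intent and why the point is minor. It does not remove the point: the sentence is something the article states, not a detail left out, and as worded it gives a different count from the general rule.

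A reader might infer three stronger things that the article does not support:

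- **That a 5-treatment sham was chosen as a design feature.** Nothing says so, and the general rule speaks against it.
- **That a promised patient blind would be broken.** The article says "physiotherapists and patients cannot be blind to intervention allocation", so the issue is matched contact and expectation only.
- **That the comparison in the stated aim is compromised.** The aim in the Background is whether the combination "can better improve the knee function and reduce pain in KOA patients than quadriceps strength training alone". HT + Q against QT involves no sham and is unaffected.

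**Conclusion.** The concern holds as an internal inconsistency in the wording of the sham schedule. Its severity is minor.

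On the likely reading the practical effect is zero, with 60 sham and 60 active treatments by week 12. On the less likely literal reading there would be 5 against 60, and the HT + Q versus ST + Q contrast would lose its matching for contact and expectation. This rests on active rTMS following the general 12-week rule, since its own sections give no other course length. Table 1 could not be checked.

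**What to change.** In the ST + Q Group section, replace the schedule sentence with:

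> *Sham rTMS will be given on 5 days in each of the 12 weeks (60 treatment days), on the same schedule as active rTMS.*

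Then check that the intervention rows of Table 1 say the same for ST + Q.

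The cost is one sentence. On the likely reading no treatments or visits are added. The Study status section describes the trial as still in preparation, so on that status the wording can be corrected before recruitment begins.

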### HT + Q Group

In the HT + Q group, the participants will receive active High-frequency rTMS and quadriceps strength training intervention with randomization of treatment order. The parameters, including noise, time, and frequency of the High-frequency rTMS, will be the same as HT groups, and the detail of quadriceps strength training will be the same as described above.

### Outcomes

Participants will be assessed by other physiotherapists blinded to the group allocation at different time points based on different assessments shown in Table 1. Additionally, baseline age, gender, symptoms, disease severity, duration, previous treatment and medication will be recorded using a questionnaire (in week 0). The primary end-point is the 12 weeks and all side effects during the study also will be recorded in real time.

### Effectiveness

#### Primary outcomes: VAS

The Visual Analog Scale (VAS) will be used as one of the primary outcomes to evaluate the improvement of knee pain, which consists of a 10-cm line, where 0 represents “no pain” and 10 represents “worst possible pain”. The participants will be asked to recall knee pain related to knee joint movement in the previous week and mark on the line. The reliability and validity of the VAS in application of musculoskeletal conditions is proved good [35]. In order to determine the clinical significance of the change in VAS score, the minimal clinically important difference (MCID) will be employed, and the MCID set as 1.16 based on previous study [36].

#### Secondary outcomes: Muscle strength

The maximal isokinetic muscle strength will be assessed by the Biodex Multi-Joint System 3 dynamometer (Biodex Medicalt, Shirley, NY, USA). Isokinetic exercise is a mode of speed-constant training, that can be used at low, moderate and high velocity for different evaluations and rehabilitation programs and provides reliable data. It is actually always used to quantify muscle strength, treatment and rehabilitation efficacy with mechanical or neurological instability of the knee or ligament injury [37].

#### Secondary outcomes: Knee Injury and Osteoarthritis Outcome Score (KOOS)

The Knee Injury and Osteoarthritis Outcome Score (KOOS, http://www.koos.nu, Chinese version) is a questionnaire that is self-administered and participants need approximately 10 minutes to answer all questions [38]. Different from Western Ontario and McMaster Universities Arthritis Index (WOMAC), KOOS has a more comprehensive assessment including five subscales: pain, symptom (stiff), activity of daily living, physical function, quality of life. Every question has a minimum score of 0 and a maximum of 4 points. After the score of each part is calculated separately, it is converted into a percentage score by the conversion formula. 0 points of the converted percentage score mean that the function of this part of the joint is very poor, while 100 points means that the function of this part of the joint is completely normal [39]. The KOOS shows good validity and reliability for patients with mild to moderate KOA [40]. The MCID of the KOOS score set as 10 based on previous study [36].

#### Secondary outcomes: 36-Item Short-Form Health Survey (SF-36)

The 36-Item Short-Form Health Survey (SF-36, Chinese version) is the secondary outcome measure which is a health-related questionnaire, and used to assess the quality of life (QOL) with high reliability and validity [41]. The scale is divided into physical health QOL and mental health QOL and includes 36 questions in total. The former consists of physical function, social function, physical role function and emotional role function, The latter contains mental health, energy fatigue, pain, and general health. The scale assesses QOL over the past month and the score of the SF-36 is 0–100 with higher scores indicating better QOL. [42]. The MCID of the SF-36 score set as 2.5 based on previous studies [43].

### Mechanism of action

#### Primary outcomes: motor cortex excitability

Transcranial magnetic stimulation (TMS) is a non-invasive brain stimulation tool and commonly used to measure the functional level of cortex excitability and physiology in vivo [44–46]. The motor evoked potential (MEP) is an important index marker of corticospinal excitability which means when magnetic stimulation over M1, the descending pathway produces excitability and contralateral muscle contraction of the recorded value. The cortical silent period (CSP) represents momentary suppression of MEP due to GABAergic. The short intracortical inhibition (SICI) and intracortical facilitation (ICF) which represent inhibitory and excitatory activation of interneurons within the motor cortex are thought to probe GABAA-mediated inhibition and glutamatergic facilitation [47].

#### Secondary outcomes: Magnetic resonance imaging (MRI)

MRI scan will use a 3.0-T GE scanner (General Electric, Milwaukee, WI, USA) with an eight-channel phased-array head coil at the Medical Imaging Department of Shanghai Seventh People’s Hospital in China. Two independent MRI scans who are radiologists trained in brain MRI measurements and having ten years of work experience will be performed on each participant at baseline and after the 12-week intervention. Before the MRI evaluation, the scanner will require the participant to rest for 10 min and participants will be asked to stay awake with eyes closed during the entire MRI scan.

Resting-state functional MRI images (Rs-fMRI) will be acquired with the following parameters: TR = 2100 ms, TE = 30 ms, flip angle = 90°, voxel size = 3.125 mm × 3.125 mm × 3.6 mm, 42 axial slices, field of view (FOV) = 200 mm × 200 mm, phases = 230. We also collected high-resolution T1-weighted structural images(T1WI), using a 3D-BRAVO sequence with the following parameters: TR = 8.2 ms, TE = 3.2 ms, flip angle = 12°, FOV = 220 mm 20 mm, Matrix = 256,256, slice thickness = 1 mm [48]. The MRI outcomes include the following: grey matter (GM) density, white matter (WM), subcortical nuclei volumes, cortical thickness; functional connectivity (FC).

The DPARSF (http://rfmri.org/DPARSF) will be used to conduct fMRI data preprocessing [49] and the FSL tools (FMRIB Software Library) will be used to process T1WI structure data analysis [50]. The volumes of neocortical GM, total GM, and WM will be obtained by SIENAX (part of FSL 5.0) [51]. The normalized volumes of subcortical nuclei volumes will be estimated from FMRIB’s integrated registration and segmentation tool (part of FSL 5.0, FMRIB Software Library) [52]. The cortical thickness will be obtained using FreeSurfer.

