In recent years, more and more evidence has proved that low activation of M1 [12] and secondary to gamma loop [13] and motor-sensory circuit disorders [14] may be potential reasons for weakness of quadricep muscles in KOA. It can be seen that the enhancement of muscle strength for KOA is not only about the improvement and optimization of muscle strength training program, but also about the activation of brain areas. Therefore, the M1 may be a potential neurotherapeutic target for therapy in KOA [15]. Furthermore, another study showed that chronic pain in KOA can also further increase motor cortex inhibition. The chronic pain in KOA patients is not necessarily related to damage to the peripheral muscular system, but rather to neuroplastic changes in pain-related circuits that result in maladaptive neuroplasticity and lead to a perpetuation of pain [16]. The neuroplasticity changes in response to constant peripheral pain and less intracortical inhibition, which leads to enhance the levels of pain and dysfunction [17, 18].

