**Fig. 1 Fig1:**
[figure not shown]
A brief flowchart of the entire study. TQPEAK, peak torque; TQPEAK/BW, TQPEAK adjusted for body weight; rTMS, repetitive transcranial magnetic stimulation; GM, grey matter density; WM, white matter; FC, functional connectivity; MRI, Magnetic resonance imaging

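### Grey matter density is a named MRI outcome, but the stated grey matter derivation is global volume by SIENAX, which is not density and is insensitive to a focal change at M1

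*Protocol article*

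**What the plan says.** The section on MRI as a secondary mechanism outcome lists what will be measured: "The MRI outcomes include the following: grey matter (GM) density, white matter (WM), subcortical nuclei volumes, cortical thickness; functional connectivity (FC"). The abstract gives the same list for the mechanism outcomes: "motor evoked potential, grey matter density, white matter, subcortical nuclei volumes, cortical thickness and functional connectivity by MRI". The Fig. 1 legend defines the abbreviation in the same way, "GM, grey matter density; WM, white matter; FC, functional connectivity", and the Table 1 footnote also expands GM as density.

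The same MRI section then says how the structural measures will be obtained:

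- In general, "the FSL tools (FMRIB Software Library) will be used to process T1WI structure data analysis".
- For grey and white matter, "The volumes of neocortical GM, total GM, and WM will be obtained by SIENAX (part of FSL 5.0").
- For the deep nuclei, "The normalized volumes of subcortical nuclei volumes will be estimated from FMRIB’s integrated registration and segmentation tool".
- For cortical thickness, FreeSurfer.

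Scans are taken at baseline and after the 12-week intervention. The Discussion describes the structural aim in terms of brain volume. On the target, the Background argues that "the M1 may be a potential neurotherapeutic target for therapy in KOA", and the HT Group section places the coil over M1 opposite the painful side, or over the left M1 when both knees are painful.

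**The concern.** The name of the outcome and the quantity to be computed are different things. Density is a voxel-wise or regional measure. A neocortical or total grey matter volume is one number for the whole structure. The article assigns a tool and a quantity to each structural measure, and the quantity assigned to grey matter is not the one in the outcome list.

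Two things are at stake. First, the team could follow the plan faithfully and still have no density result, or could report total volume under the density label. The choice between the two quantities would then be open until after the results are known. Second, the treatment is aimed at one region in one hemisphere. A global total mostly reflects tissue outside that region, so an unchanged total would say little about M1 structure.

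**Working it through.** **1. Is there a planned figure to reproduce?** None is given for any MRI outcome. The Sample size calculation section works from pain: effect size 0.24, 4 groups, 6 measures, alpha 0.05, power 0.80. For the between-groups factor of a repeated-measures ANOVA, the noncentrality is

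λ = f² × N × m / (1 + (m − 1)ρ).

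The article gives no correlation; ρ = 0.5 is assumed here. With N = 116, λ = 0.0576 × 116 × 6 / 3.5 = 11.45 on 3 and 112 degrees of freedom, and power is 0.806. Searching in steps of four, 116 is the smallest total that reaches 0.80. Allowing for 20% drop-out, 116 / 0.8 = 145, which rounds up to 37 per group, or 148. The plan's figure reproduces, and nothing about MRI enters it.

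**2. Named outcome against stated derivation.**

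| Outcome as listed | Derivation stated in the MRI section | Match? |
|---|---|---|
| Grey matter density | SIENAX: neocortical and total grey matter volume | No: volume, not density |
| White matter (no metric named) | SIENAX: volume | No conflict |
| Subcortical nuclei volumes | FSL registration and segmentation tool: normalised volumes | Yes |
| Cortical thickness | FreeSurfer | Yes |
| Functional connectivity | DPARSF preprocessing of the fMRI data | No conflict |

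The mismatch is confined to the first row. The general sentence on FSL tools neither names a density step nor excludes one.

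**3. How a global total responds to a focal change.** Let s be the share of grey matter in the focal region and c the percentage change there, with the rest unchanged. The total then changes by s × c. The article gives neither quantity. The ranges below are assumptions for illustration.

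| Share s | c = 2% | c = 5% |
|---|---|---|
| 0.5% | 0.01% | 0.025% |
| 1% | 0.02% | 0.05% |
| 2% | 0.04% | 0.10% |
| 5% | 0.10% | 0.25% |

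Whatever the local change, the total shows only the fraction s of it: one two-hundredth at s = 0.5% and one-twentieth at s = 5%. This applies to the SIENAX totals. It does not apply to cortical thickness or functional connectivity read regionally.

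**The case against.** The strongest reply is that a journal article condenses the full protocol. The voxel-based step, the region of interest and the processing stream are details that may stand elsewhere. This is fair as far as missing detail goes. It does not remove the conflict, because the article does state a quantity for grey matter, and that quantity is not the named outcome.

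A second reply is that the protocol nowhere offers total volume as its test of M1. The primary mechanism outcome is motor cortex excitability, the planned correlations use MEP and functional connectivity, and the structural aim is worded broadly as brain volume. This also stands. It limits the dilution point to a caution about what a grey matter total can support. It also shows why renaming the outcome is an acceptable remedy.

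Some stronger readings are tempting, and the article does not support them:

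- A reader might infer that the pipeline gives nothing beyond whole-brain grey and white matter volumes. It also gives subcortical volumes and cortical thickness, and thickness can be read by region, although no region is named.
- A reader might infer that density is out of reach. T1 images with 1 mm slices are planned and FSL is the named software, so the step is unstated, not impossible.
- A reader might want to set the diluted signal against scan noise. That needs a scan-rescan error that the article does not give, and a single-scan error would be the wrong yardstick for a comparison of arms of 37.
- A reader might infer that SIENAX is unsuited to measuring change over time. Nothing in the article establishes this.

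**Conclusion.** The concern holds as a conflict between label and measure. Four places in the article name grey matter density; the MRI section derives neocortical and total grey matter volume. These totals are not density and pass on only a small fraction of any change confined to M1: 0.01% to 0.25% of the total under the assumed shares and local changes above. The conflict itself rests on no assumption. The size of the dilution rests entirely on those two assumed ranges and on no change occurring elsewhere.

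The consequence is limited. One secondary mechanism outcome is affected. The VAS analysis, the sample size of 148, motor cortex excitability, functional connectivity, cortical thickness and the subcortical volumes are not.

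**What to change.** Choose one of two courses before data are collected; the Study status section describes the trial as still in preparation.

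1. Keep density. State that it will be derived from the planned T1 scans by voxel-based morphometry in FSL, and prespecify M1 of the target hemisphere as the region in all four arms. In the arms without active stimulation, define the target hemisphere by the rule already given for the HT group (opposite the painful knee, left if both are painful), so that the region is comparable across arms. Keep the SIENAX totals as descriptive.
2. Keep SIENAX. Rename the outcome grey matter volume in the abstract, the Fig. 1 legend, the Table 1 footnote and the MRI section, and draw no M1-specific structural conclusion from it.

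The first course costs a little extra analysis time on scans and software already planned. The second is a wording change, at the price of giving up a regional grey matter density result. Neither needs extra scanning.
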